### Cognitive adaption training nurses and specialists

Nurses in the intervention teams are responsible for setting up and evaluating the intervention for a maximum of one to three patients, while all nurses are responsible for supporting the daily use of interventions of all patients. Hereafter, the term CAT case manager refers to the former role, while the term nurse refers to the general tasks of all nurses in the team. CAT specialists are professionals educated to at least bachelor level, who have knowledge about the relationship between cognition and general functioning, and who are knowledgeable with regard to the underlying principles of CAT. Besides supervising CAT case managers in the development and implementation of the intervention for each individual patient, CAT specialists guard the underlying principles of CAT in the interventions that are applied. CAT specialists APMS and JER, both psychologists at Lentis Psychiatric Institute, were trained by [name], the developer of CAT. They provided additional training for CAT specialists at the other institutions.

### Blinding

Blinding will take place at the level of assessors of outcome variables. Blinding of patients and nurses is not possible due to the nature of the intervention. Similarly, blinding of the researcher is not possible due to the researcher’s (APMS) role in the training of nurses and CAT meetings with nurses. Research assistants (psychology students educated to at least bachelors level) are trained to administer the assessments. They are blind to the treatment arm in which the patient is included and do not receive any information with regard to the content and aims of the intervention. Nurses and patients are requested not to disclose any information about the allocation of conditions or the content of the intervention to the students. Students are instructed to inform the researcher immediately when they suspect blinds are broken, in which case the measurement is finished by another student who is still blind to the allocation of the patient. Furthermore, guessing of the allocation group by raters after each assessment will be used to evaluate whether blinding was successful.

### Tests and measures

#### Testing procedure

All participants (intervention and control group) are measured at baseline and after three, six, nine and 12 months. Additionally, to determine whether any obtained results in the intervention group can be retained, follow-up assessments are planned after 15, 18, 21 and 24 months. Although CAT is not designed to alter cognitive functioning (rather to bypass cognitive problems) nor to improve symptoms, cognitive functioning and symptomatology are measured again at six and 12 months to evaluate any unexpected changes. The schedule of enrollment, interventions and content of the assessments is shown in Table 1. For all patients, interviews and cognitive tests are assessed in separate sessions. In the intervention group, environmental and functional problems in everyday functioning are assessed in an additional session. Level of everyday functioning is chosen as the primary outcome. All tests and measures are described below. Secondary outcome measures are quality of life, empowerment and apathy. Assessment outcomes for the control group will not be used in their treatment plan for the duration of the trial.

**Table 1 Tab1:** **Schedule of enrollment, interventions and assessments**

	**Study period**									
		**Intervention period**					**Follow-up** ^**b**^			
**Time point** ^**a**^	**< T** _**0**_	**T** _**0**_	**T** _**3**_	**T** _**6**_	**T** _**9**_	**T** _**12**_	**T** _**15**_	**T** _**18**_	**T** _**21**_	**T** _**24**_
**Enrollment:**										
Randomization	X									
Informed consent		X								
**Groups:**										
Control (TAU)		X	X	X	X	X				
Intervention (TAU + CAT)^c^		X	X	X	X	X	X	X	X	X
**Assessments:**										
Environmental/functional problems^b^ and behavior type		X								
Clinical and cognitive characteristics		X		X		X				
Demographical information		X								
Everyday functioning		X	X	X	X	X	X	X	X	X
Quality of life and empowerment		X		X		X				
Apathy		X		X		X				
Healthcare costs		X	X	X	X	X	X	X	X	X

^a^Number illustrates number of months after baseline.

^b^Assessed for the intervention group only.

^c^
*Abbreviations*: *TAU* treatment as usual, *CAT* Cognitive Adaptation Training.

#### Demographical information

Demographical information (date of birth, gender, nationality, level of education, main diagnosis, comorbid diagnoses, age of onset, psychiatric disorders of parents and siblings, relevant medical events, neurological disorders and alcohol and drug use) is partly obtained from the patient file and completed at baseline assessment (T0).

#### Severity of current psychotic symptoms

The presence and severity of psychotic symptoms is measured using the Positive and Negative Syndrome Scale (PANSS) [16] by trained blind raters (psychology students educated to at least bachelors level). The PANSS is a semi-structured interview that consists of three subscales: positive symptoms, negative symptoms and general psychopathology. The PANSS is a widely used instrument with good psychometric properties [16]. The PANSS is administered for patients with a psychotic disorder or a disorder with psychotic features only.

#### Behavior type

The Frontal Systems Behavior Scale (FrSBe) [17], which is filled out by the CAT case manager, is used to determine the behavior type. This scale consists of 46 statements on apathy, disinhibition and executive functioning. Each statement can be scored on a scale ranging from one (almost never) to five (almost always). The apathy and disinhibition scores determine whether the patient’s behavior type is best characterized as apathy, disinhibition or mixed (combination of apathy and disinhibition).

#### Executive functioning

The level of executive functioning is determined with the Modified Card Sorting Test (MCST) [18] and the letter fluency task [19]. The perseveration and categories score of the MCST and the total score of the letter fluency task are used to determine the level of executive functioning. A division is made between poor (problems with planning and performing the steps of basic everyday tasks such as showering and dressing) and fair (problems on higher level functions, such as management of money and work skills). When the participant is not able or willing to participate in the tests, the score on the executive subscale of the FrSBe is used to determine the level of executive functioning.

#### Cognitive strengths and weaknesses

Complementary cognitive tests are administered to determine strengths and weaknesses in visual attention (Picture Completion; Wechsler Adult Intelligence Scale IV (WAIS-IV)) [20], auditory attention (Digit Span forward; WAIS-IV) [20], working memory (Digit Span Backward; WAIS-IV) [20] and verbal short term memory (Word Learning Task) [21]. Strengths and weaknesses in auditory attention and working memory are determined with cut-off scores identical to those used by [name] (personal communication, [name]) (auditory attention: <4 = weak, >7 = strong and 4 to 7 = average; working memory: <2 = weak, >5 = strong and 2 to 5 = average). For visual attention, we use transformed raw scores to scale scores on the picture completion task according to the Dutch norms [20] and set cut-off points for the scale scores (<5 = weak, >10 = strong and 5 to 10 = average). Finally, for verbal short term memory, we use the available Dutch norms [21] to set cut-off points at percentiles (<25 = weak, >50 = strong and 25 to 50 = average).

#### Environmental and functional assessment

The individual problems with everyday functioning are assessed with the Environmental and Functional Assessment (EFA) by Velligan *et al*. [10]. The EFA is an extensive interview on daily activities, functional skills and the presence of necessary skills to perform these activities. We slightly adjusted the EFA so that the given examples reflect situations that are common for the study population in the Netherlands. In addition, we now explicitly ask for the patient’s wishes with regard to the every tasks. The EFA is administered in the patient’s residence by a CAT specialist together with the CAT case manager. If necessary, the CAT case manager supports the patient in answering the questions during the interview.

#### Everyday functioning

Level of everyday functioning is measured with a number of instruments. First, the Multnomah Community Ability Scale (MCAS) [22] is used to enable us to compare results with previous CAT studies. The MCAS is a semi-structured interview containing 17 items and assesses a variety of domains of community adjustment. As reports of mental healthcare professionals who are in frequent contact with patients tend to be more linked to performance on everyday tasks than self-reports [23], a comparison of patients’ reports and nurses’ observations (measured with observational questionnaires described below) is used to determine possible discrepancies between answers and to adapt MCAS scores if necessary. The instrument was translated into Dutch (PQ) and back-translated by a professional translator. The English version has proven to be reliable and valid [24].

The second instrument used to measure everyday functioning is the Social and Occupational Functioning Scale (SOFAS) [25]. The SOFAS is a reliable and valid instrument for measuring social, occupational and interpersonal functioning on a single-item scale (range: 0 to 100) [26].

Third, engagement in work-related activities is used as an indication of everyday functioning. Engagement in work-related activities is measured in number of partial days a week (a partial day consists of three hours) and is registered daily by the staff.

#### Quality of life

Quality of life is measured with the Short Form Health Survey (SF-12) [30]. The SF-12 is a self-report questionnaire with 12 items measuring subjective physical, psychological and social well-being. The SF-12 has good psychometric properties for use in SMI populations [31].

#### Empowerment

Empowerment is measured by a self-report questionnaire, the Dutch Empowerment Questionnaire ((DEQ) *Nederlandse Empowerment vragenLijst*) [32]. Three of the six subscales are used in the current study, namely professional help, self-knowledge and belonging. Items are scored on a five-point scale ranging from one (strongly disagree) to five (strongly agree). The validity and reliability of the DEQ is sufficient [32].

#### Apathy

The avolition-apathy subscale of the Scale for the Assessment of Negative Symptoms (SANS) [33] is administered to measure apathy. The four items of this subscale can be rated from 0 (absent) to four (severe). The SANS is a valid and reliable instrument [34].

Motivation to engage in activities is assessed using the motivation subscale from the Negative Symptom Assessment, a semi-structured interview (NSA-16) [35]. The motivation subscale contains four items that can be rated from one (no evidence of this symptom) to six (severe). The validity and reliability of the NSA-16 is good [36].

### Treatment as usual

Although the institutions vary somewhat in the treatments they offer, all patients have access to pharmacotherapy. The range of psychological, psychosocial and non-verbal therapies (such as psycho-education, cognitive behavioral therapy, Liberman training, peer support groups, psychomotor therapy, music therapy, creative arts therapy and sports groups), as well as educational or work projects (such as a framing center, graphic design and copy center, a farmhouse, catering and site and garden maintenance) differs somewhat between locations, which will be accounted for in the analyses. For each patient, treatment is aimed at a combination of therapies and daily activities that best matches the needs, goals and wishes of the patient in order to reach an optimal recovery process. Treatment and progress are evaluated at least once per year.

### Cognitive adaptation training: the intervention

#### Preparation: training of nurses and cognitive adaptation training specialists

To optimize the implementation of CAT and to ensure CAT would be included in the working routine, all nurses in the intervention groups were trained in CAT, though not screened for eligibility. Nurses participate in a didactical group training prior to the recruitment of patients. The training is delivered by the CAT specialists who were trained in CAT by [name], the developer of CAT (APMS and JER). Translated PowerPoint presentations and video demonstrations of [name] serve as the basis of the didactical training, to ensure fidelity to the CAT treatment model. The didactical training includes the theoretical background and principles, assessments, use of the CAT manual, intervention strategies, CAT visits and continuity of the intervention. APMS and JER provided an additional training on assessing the EFA, composing the CAT treatment plan (see below) and continuity of CAT in daily care for the CAT specialists at all intervention locations.

#### Designing the cognitive adaptation training treatment plan

The protocol developed by [name] and her group (personal communication, [name], [name]) is followed to design the CAT treatment plan, with some minor modifications due to the availability of tests translated into Dutch. The CAT plan and starting point of the intervention is based on: (1) behavior type, (2) level of executive functioning, (3) goals for improving everyday functioning and (4) cognitive strengths and weaknesses that are assessed at T0. Upon completion of this assessment, a CAT specialist summarizes the outcomes of the cognitive assessment and discusses these with the CAT case manager during the first CAT meeting. Based on the wishes and problems reported by the patient during the EFA, the CAT specialist and the CAT case manager discuss the priority of problems and make an initial priority of goals that may be targeted with the intervention. In the next step of the intervention process, the CAT case manager discusses the assessments with the patient during the first CAT visit. The patient is encouraged to formulate their own goal, however if they are unable to do so, the CAT case manager suggests a goal according to the priority of the initial CAT plan. If necessary, the priority on the CAT plan is adapted following the wishes of the patient after the first or subsequent CAT visits.

#### Implementing the cognitive adaptation training treatment plan

Once the CAT treatment plan is formed and discussed with the patient, the CAT specialist and CAT case manager discuss possible interventions using the CAT manual and taking individual characteristics into account. Possible intervention strategies are discussed and set up together with the patient when in any way possible. Intervention strategies are limited to one goal at a time to ensure patients are not faced with more than they can handle. After the first intervention the CAT case manager is responsible for setting up and organizing environmental supports and evaluating the interventions with the patients in their caseload. CAT visits to the patients are planned within the daily routine of the nurses. Based on our pilot study, a duration of CAT visits of approximately 45 minutes a week per patient in total (time may be divided over a number of CAT visits) is deemed to be sufficient. In addition, the CAT case manager makes a record of the CAT visits in the patient file, based upon four questions: what interventions worked, what interventions did not work, what changes are made in the intervention strategies and what issues need to be kept in mind.

During the implementation phase (one to two months), the CAT specialist and CAT case manager plan CAT discussion meetings at least once a month. The nursing team as a whole is informed of, and responsible for, and supports the daily use of the interventions of all patients (for example, checking and reporting on whether a recorded message leads to the targeted behavior, or changing a weekly checklist). In the securing phase (up to 12 months), CAT group meetings are incorporated into regular staff meetings for at least another six months, to stimulate the exchange of knowledge and interventions between nurses. Finally, after the securing phase (after 12 months), a CAT focus group including the researchers and clinicians (APM, JER and LM) and a delegation of nurses, will determine the form and frequency of CAT meetings in the follow-up phase (12 to 48 months).

### Statistical analysis plan

#### Primary and secondary outcomes

Mean differences in the outcomes between the intervention and control group will be investigated by applying a marginal linear mixed model (modeling mean scores for both groups) using restricted maximum likelihood estimation to the outcomes at each time point after baseline. The analyses are corrected for baseline scores to eliminate the effect of possible (average) differences between the intervention and control group at baseline. The treatment effect is essentially estimated for each time point by subtracting the estimated mean scores of the control group from the estimated mean scores of the intervention group, reflecting the estimated mean difference between the groups over time.

Sub-analyses will be performed to evaluate individual improvement in everyday functioning. To this end, we will specifically evaluate only those items of the MCAS, SFS and LSP that measure the domain(s) that are recorded as goals in the CAT treatment plan. That is, we will evaluate whether patients have indeed improved on the activities they have been working on with CAT, and for which individually tailored interventions were set up. Sum scores of items of the LSP, and SFS reflecting a certain goal will be computed. Differences in these sum scores over time will reflect whether patients’ performance on these domains have improved, did not change or have deteriorated. Generalized linear models will be used to determine whether there is a statistically significant proportion of improvement target behaviors compared to no change or deterioration.

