### Sample size calculation

This sample size is based on a power analysis using the effect size (0.79) calculated from Multnomah Community Ability Scale (MCAS) scores from our pilot study [12]. To detect a significant change in daily functioning measured by the MCAS with α set at 0.05 and a power of 0.9, 35 patients should complete the intervention. Studies have shown that withdrawal from psychosocial interventions in psychiatric patients can be substantial. Therefore we have taken into account a conservative drop-out rate of 30% and will include at least 50 patients in each condition. Analyses are performed when both groups completed the assessments at 12 months and at the study end when follow-up assessments of the intervention group have been completed (24 months).

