### Randomization

With regard to the randomization procedure, several issues were to be considered. Each location employed several nursing teams, with separate offices, patient units and caseloads. Cluster randomization was applied on a nursing team level for each of the three institutions. This resulted in an equal distribution in the number of nursing teams allocated to CAT and TAU within each institution. Not only does this approach prevent contamination between nurses in the intervention and control groups, it also enhances implementation of the intervention since all nurses within each intervention team are trained in CAT and regular nursing meetings can be used for informing colleagues about the progression of the intervention. The nursing teams are randomly allocated to either the intervention or the control group by an independent staff member (without interest in or knowledge about the outcome of the allocation) who blindly draws a ticket from a basket containing a CAT ticket and a blank ticket. No inclusion or exclusion criteria are applied for nurses.

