#### Cost-effectiveness and cost-utility analysis

The primary outcome measure of the planned cost-effectiveness analysis (CEA) is the MCAS. Results of the CEA are expressed in terms of incremental costs per point change in MCAS score. Furthermore, a cost-utility analysis will be conducted with quality adjusted life years (QALY) as the primary outcome measure. In order to estimate QALYs, utility scores are derived from the SF-12 [38]. The uncertainty surrounding the cost-effectiveness and cost-utility ratios will be estimated by bootstrap analyses. In addition, cost-effectiveness acceptability curves will be used to inform decision-makers on the probability that CAT is cost-effective.

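### Nursing teams were randomized, but the stated analysis model has no nursing-team term; if outcomes correlate within teams, the 5% error rate is not kept

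*Protocol article*

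**What the plan says.** On allocation, the Randomization section states: "Cluster randomization was applied on a nursing team level for each of the three institutions". It adds: "This resulted in an equal distribution in the number of nursing teams allocated to CAT and TAU within each institution". The teams are described as distinct working units: "Each location employed several nursing teams, with separate offices, patient units and caseloads". The Design section calls the study a cluster randomized trial, and the opening of Methods/Design cites the CONSORT extension for such trials.

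On analysis, the section Primary and secondary outcomes, under the heading Statistical analysis plan, says that group differences will be investigated "by applying a marginal linear mixed model (modeling mean scores for both groups) using restricted maximum likelihood estimation", at each time point after baseline. The one adjustment named there is for baseline: "The analyses are corrected for baseline scores to eliminate the effect of possible (average) differences between the intervention and control group at baseline". Nursing team does not appear in that section.

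The only other grouping factor comes under Treatment as usual, where the range of therapies and work projects "differs somewhat between locations, which will be accounted for in the analyses". The Randomization section says that each location has several teams, so location means institution here.

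On uncertainty in the economic evaluation: "The uncertainty surrounding the cost-effectiveness and cost-utility ratios will be estimated by bootstrap analyses". The resampling unit is not given.

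**The concern.** When teams are allocated, the treatment contrast is a contrast between teams. Patients of one team live in the same unit and have the same nurses. In the CAT arm the whole team supports the daily use of every patient's interventions (Implementing the cognitive adaptation training treatment plan). Some correlation of outcomes within a team is therefore plausible.

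The standard error of the treatment effect has to include the between-team variance, and its degrees of freedom have to reflect the number of teams. A repeated-measures model of group means with only a within-patient covariance does neither. Adjusting for institution does not repair this, because differences between teams within an institution remain.

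At stake are the p-values and confidence intervals of the primary comparison and of the secondary outcomes that use the same model. A difference between a limited number of teams could be reported as an effect of CAT.

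**Working it through.** **1. The plan's own figure.** Inputs from Sample size calculation: effect size 0.79, alpha 0.05, power 0.90, 35 completers (read as per arm, because 50 per condition follows from it), 30% dropout. A two-sided, individual-level two-sample t test has noncentrality 0.79 × √(n/2).
- n = 34 per arm: power 0.894.
- n = 35 per arm: noncentrality 3.305, power 0.903.
- 35 / 0.70 = 50 per arm, 100 in total.

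The figure reproduces with patients as independent units and no design effect. The sample size therefore gives no sign that clustering was allowed for.

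**2. Number of teams.** It is not stated. Equal numbers of teams per arm in each of three institutions require at least 2 × 3 = 6. I take 6, 12 and 24 as assumed values.

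**3. Error rate if teams are ignored.** Take 70 completers (2 × 35) in K equal teams, so m = 70/K. The ICC is not in the document; 0.02 to 0.10 is assumed.
- Design effect: DE = 1 + (m − 1) × ICC.
- Reported SE as a fraction of the true SE: 1/√DE.
- True two-sided error of the nominal 5% test: 2 × [1 − Φ(1.96/√DE)].

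| Teams (m) | ICC | DE | SE fraction | True error |
|---|---|---|---|---|
| 6 (11.7) | 0.02 | 1.21 | 0.91 | 0.075 |
| 6 | 0.05 | 1.53 | 0.81 | 0.113 |
| 6 | 0.10 | 2.07 | 0.70 | 0.173 |
| 12 (5.8) | 0.02 | 1.10 | 0.95 | 0.061 |
| 12 | 0.05 | 1.24 | 0.90 | 0.079 |
| 12 | 0.10 | 1.48 | 0.82 | 0.108 |
| 24 (2.9) | 0.02 | 1.04 | 0.98 | 0.054 |
| 24 | 0.05 | 1.10 | 0.96 | 0.061 |
| 24 | 0.10 | 1.19 | 0.92 | 0.073 |

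Example: 6 teams, ICC 0.05 gives DE = 1 + 10.67 × 0.05 = 1.53; 1.96/√1.53 = 1.58; error 0.113.

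Simulation of an ordinary t test under no effect (20,000 runs per scenario) agrees. With 6 teams it gives 0.114 at ICC 0.05 and 0.176 at ICC 0.10; with 12 teams, 0.078 and 0.110. At ICC 0 the error is 0.048 and 0.049, so there is no inflation without within-team correlation.

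The 70 is itself an assumption. If all 100 enrolled patients contributed, teams would be larger and the figures higher: with 6 teams and ICC 0.10, DE is 2.57 and the error 0.221.

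**4. Power of a valid analysis.** With 70 completers and ICC 0.05, a team-level t test with K − 2 degrees of freedom has power of about 0.53 with 6 teams, 0.76 with 12 and 0.855 with 24. Adding institution as a fixed effect uses two more degrees of freedom. With 6 teams that leaves 2, a critical t of 4.30 against a noncentrality of 0.79/√(1.533 × 2/35) = 2.67, and power of about 0.33.

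**The case against.** **The article does not exclude a team term.** It gives no covariance structure at all, not even for repeated measures within a patient, which the model must have. A marginal model fitted by REML can carry a team-level covariance. The authors knew that the design was clustered, and a condensed article may leave such detail to a fuller plan. This stands as a limit on certainty: a reader might infer that the standard errors will be too small as a matter of fact, and the text does not establish that. It does not remove the point. The section states model, estimator, adjustment and estimand, another section names location as a factor to account for, and the sample size treats patients as independent. The randomized unit is missing from all three.

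**The size may be small.** This also stands. The 11% to 17% figures belong to 6 teams at ICC 0.05 to 0.10. The article says several teams per location, and a larger number shrinks the effect. The calculation is for one time point and does not remove between-team variance explained by baseline score or location, so the residual ICC may be lower.

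**Shared raters.** A reader might infer that a team's patients are all scored by one nurse. The Everyday functioning section does not support this: in the CAT arm each nurse completes the questionnaires for one to three patients. The MCAS, on which the sample size rests, is an interview, and the Blinding section has trained research assistants administering the assessments. The point rests on shared units, nurses and delivery.

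**Bootstrap and generalized linear models.** It is tempting to say that these have the same fault. The bootstrap unit is not stated, so that point is only conditional. The generalized linear models concern goals recorded in CAT treatment plans and are not described as a comparison of the randomized arms, so the point does not extend to them.

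**Conclusion.** The stated analysis does not match the stated randomization, and this should be corrected. The omission is certain on the face of the article; the error inflation is conditional on a within-team ICC above zero.

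Under the assumptions of 70 completers, equal team sizes and ICC 0.02 to 0.10, the true error of the nominal 5% test is about 7.5% to 17% with 6 teams, 6% to 11% with 12 and 5% to 7% with 24, before any reduction from baseline and location adjustment. The documents do not show which of these applies, and they do not support quoting the 6-team figures as the expected result.

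**What to change.** - Keep the baseline-corrected repeated-measures model. Add a random intercept for nursing team, in addition to the within-patient covariance, and institution as a fixed effect because allocation was done within institution.
- Make Kenward-Roger or Satterthwaite degrees of freedom the primary inference. Retain the team term even if its variance is estimated at zero.
- Report the number of teams per arm and institution, and the estimated ICC.
- If the economic bootstrap compares the randomized arms, resample by team within institution, and state that this is unreliable with very few teams.
- Do not require confirmation by a team-level permutation test within institution when teams are few. Six teams (2 + 2 + 2) allow 2 × 2 × 2 = 8 allocations, so the smallest two-sided p is 2/8 = 0.25. Eight teams (4 + 2 + 2) allow 6 × 2 × 2 = 24, so the smallest is 2/24 = 0.083. Neither can reach 0.05.

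The change needs a few sentences in the plan and a few lines of code; team membership is known from the allocation. It should be settled before the 12-month analysis. The real cost is wider intervals and, with few teams, power well below the stated 0.90, which the plan should acknowledge.

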Possible weaknesses of the study are the lack of measurements focusing on the nurses who carry out the intervention. Motivation, self-efficacy and empowerment of the nurses may mediate the effect of the intervention, but an absence of appropriate instruments in this regard leaves us unable to take these aspects into account. Moreover, there are few instruments that are specifically designed for measuring everyday functioning of patients residing in long-stay clinical facilities, whose problems and needs may differ from patients living in the community. Finding a suitable instrument is further complicated by the fact that areas for interventions are individually determined and therefore differ for each patient. Due to the global nature of the measures of everyday functioning, our instruments may not be sensitive enough to assess improvements because CAT aims to improve one or two areas of functioning at a time. For this reason, we included the additional sub-analyses in the statistical analysis plan that specifically evaluate improvements in targeted domains (as described in the statistical analysis section).

If evidence yields support for CAT, this may fulfill a need for a hands-on intervention that can contribute to the functional recovery of patients living in long-stay clinical facilities.

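### The goal-specific sub-analysis counts unchanged target behaviors against CAT, so on its natural reading it tests whether more than half improved, not whether there was net improvement

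*Protocol article*

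**What the plan says.** Under Statistical analysis plan, Primary and secondary outcomes, the Protocol article adds sub-analyses of individual improvement. They use only those items that "measure the domain(s) that are recorded as goals in the CAT treatment plan". The question is put plainly: "we will evaluate whether patients have indeed improved on the activities they have been working on with CAT". Item sums are formed for each goal, and "Differences in these sum scores over time will reflect whether patients’ performance on these domains have improved, did not change or have deteriorated". The three categories then enter a test by generalized linear models, intended to "determine whether there is a statistically significant proportion of improvement target behaviors compared to no change or deterioration".

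The section gives no reference proportion for this test and describes no comparison with the control group. The interview on which the goals are based belongs to one arm only: "In the intervention group, environmental and functional problems in everyday functioning are assessed in an additional session" (Testing procedure; Table 1 marks it as intervention group only).

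The Discussion explains why the sub-analysis exists. The global scales may fall short: "our instruments may not be sensitive enough to assess improvements because CAT aims to improve one or two areas of functioning at a time".

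**The concern.** The question is about improvement, and the outcome has three levels. The contrast puts the middle level on the side of failure. A target behavior that stays the same then counts against CAT exactly as one that worsens.

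Within one arm, setting a category against its complement is a test of p = 1 − p, that is, p = 0.5. It is also what the intercept of a binomial logit model tests by default. Absence of net improvement corresponds to 50% improved only if no score is unchanged.

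Some ties are to be expected. The scores are short item sums, LSP items have four points, and the Discussion describes rehabilitation in these patients as slow. The sub-analysis could therefore fail to show a benefit in the situation for which it was added.

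**Working it through.** **Inputs from the Protocol article.** 35 completers, 50 enrolled per arm, effect size 0.79, α = 0.05, power 0.90, 30% drop-out (Sample size calculation). Three outcome categories and the pooled contrast (Primary and secondary outcomes).

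**Assumptions.** Two-sided 5%; one target behavior per completer, all independent; the shares improved, unchanged and deteriorated, which the article does not give.

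**Step 1. The article's own figure.** A two-sample t calculation with effect size 0.79, two-sided α = 0.05 and power 0.90 gives 34.66, hence 35 per arm; 35/(1 − 0.30) = 50. The sample size reproduces. It concerns the MCAS comparison; the sub-analysis has no figure of its own.

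**Step 2. What the two tests ask.** Let t be the unchanged share and s the improved share among changed scores. Then improved = (1 − t)s and deteriorated = (1 − t)(1 − s).
- Pooled contrast at odds = 1: the null is improved = 0.5.
- No net improvement: s = 0.5, so improved = (1 − t)/2. This is 0.40 at t = 0.20 and 0.35 at t = 0.30.

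The two nulls coincide only at t = 0.

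**Step 3. Critical counts.** In the exact two-sided binomial test against 0.5 with n = 35, significance for improvement needs at least 24 improved (69%). A count of 11 or fewer (31%) is significant in the wrong direction. With n = 50 the limits are 33 and 17.

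**Step 4. Power under a 4:1 benefit (s = 0.8), n = 35.** Pooled power is P(X ≥ 24) for X ~ Bin(35, 0.8(1 − t)). The comparator is the exact sign test on changed scores.

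| Unchanged | Improved | Deteriorated | Pooled vs 0.5 | Improved vs deteriorated |
|---|---|---|---|---|
| 0% | 80% | 20% | 97% | 97% |
| 20% | 64% | 16% | 35% | 89% |
| 30% | 56% | 14% | 9% | 84% |

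With 50 target behaviors the pooled test has 45% and 10% power at 20% and 30% ties, against 98% and 95%.

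**Step 5. Wrong-direction results, n = 35: P(X ≤ 11).**

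| Unchanged | 4:1 benefit | 3:1 benefit |
|---|---|---|
| 19% | 0.01% | 0.04% |
| 33% | 0.7% | 1.9% |
| 40% | 3.5% | 7.3% |
| 50% | 20% | 29% |

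**Step 6. How many ties?** An assumed model of 2 to 4 four-point items (item SD 0.9, inter-item correlation 0.4, retest correlation 0.7) gives about 19–33% ties when nothing changes on average. A similar model with a 0.5 SD benefit (about 4.6–4.9 improved per deteriorated) gives 15–27%. At 4:1 and n = 35, pooled power is 55% at 15% ties and 15% at 27% ties, against 91% and 85% for the sign test.

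**Step 7. An illustration with many ties.** Take 50 target behaviors: 17 improved, 29 unchanged (58%), 4 deteriorated. Pooled: 17/50 against 0.5, p = 0.033, in the unfavourable direction. Improved versus deteriorated: 17 of 21, p = 0.007, favourable. The tie share lies outside the modelled range, so this shows the mechanism and is not a forecast.

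**The case against.** The strongest reply is that the value 0.5 appears nowhere. The article names a model family and leaves out the reference value, link and form of test, which an article may leave to a fuller plan. **This stands in part:** the 50% null is an inference. The contrast itself, however, is written, and other readings do not rescue it. Against 0% almost any data would pass. The value (1 − t)/2 depends on an unknown tie share. If improvement were contrasted with each other category separately, improved versus unchanged would still count stability against CAT.

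Second, counting unchanged as not improved is an ordinary responder definition, and a finding that fewer than half improved would then be correct. **This is a fair alternative estimand,** but the article states no majority threshold and gives no reason for one. A reader might infer that the test's downward rejections under equal improvement and deterioration (20% and 40% at 20% and 30% ties) are false-positive rates. The article never states that equality as its null, so they cannot be called that.

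Third, a reader might infer that the test is likely to reverse a real benefit. The documents do not support this. They give no tie rates, and within the modelled 19–33% a significant reversal occurs in 2% of trials or fewer.

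Fourth, the alternative has faults. A sign test ignores ties: 6 improved, 44 unchanged and none worse gives p = 0.031 with only 12% improved. Goals are also chosen from reported problems at baseline, so regression to the mean could produce net improvement without CAT. **Both stand** and shape the remedy. Patients may also have several goals over the year, so 35 behaviors is only one scenario.

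**Conclusion.** The concern holds in a limited form. The written contrast does not match the written question, because it counts unchanged target behaviors against CAT. On the natural within-arm reading, the cost is power: about 35% to 9% at 20–30% ties, against 89% to 84% for improved versus deteriorated. These figures rest on 35 independent target behaviors, a 4:1 benefit, two-sided 5%, and assumed tie rates; with fewer ties the loss is smaller, and with none it vanishes.

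It would go too far to say that the protocol fixes a 50% null, or that the test will probably point the wrong way. Even a significant result below one half would mean that fewer than half improved, not that CAT harmed patients.

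Only the supplementary sub-analysis is affected; the primary mixed model and the sample size are not. It still merits correction, because the Discussion relies on it if the global scales prove too insensitive.

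**What to change.** In Primary and secondary outcomes, replace the pooled contrast. Analyse the signed change in the goal-specific sum score, or the three ordered categories, against a null of zero shift. Give improved versus deteriorated as a supporting test, not the main one, because it can be significant with few improvers. Report the shares improved, unchanged and deteriorated beside it. If a majority-improved criterion is in fact intended, state the 50% reference and the reason for it.

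Add that the result is a within-arm change, open to regression to the mean, and must not be read as a CAT effect without a control comparison.

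The cost is a few sentences of analysis wording, best settled before the 12-month analysis. No new data or patients are needed.
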